## Abstract

**Background:**

Uterine leiomyomas are common for reproductive-aged women and affect women’s quality of life due to heavy menstrual bleeding or dysmenorrhea. Leiomyomas grow according to estradiol exposure and decrease after post-menopause. In case serious symptoms are caused by leiomyomas, pharmacotherapy or surgical treatment is proposed. Prior to surgical treatment, pharmacotherapies aimed at the reduction of leiomyoma and uterine volume or improvement of anemia are introduced to conduct minimum invasive surgery (i.e., to reduce blood loss or surgical duration). Recently, relugolix (40 mg orally once daily) as a gonadotropin-releasing hormone (GnRH) receptor antagonist has proved its sufficient efficacy in suppressing estradiol levels without the transient estradiol flare-up compared with GnRH agonist. However, long-term administration should not be permitted liable to for climacteric disorder or osteoporosis, and evidence is lacking on the actual efficacy and extent of adverse effects of the every-other-day dosing regimen. This trial aimed to prove non-inferiority in volume reduction effect on leiomyoma and safety (i.e., reduction of adverse effects) by every-other-day administration after 2 months of everyday administration compared to daily administration throughout the duration.

**Methods:**

A minimization adaptive randomized control trial (RCT) will be conducted. Patients (over 20 years old) harboring leiomyoma who will be undergoing surgical treatment will be invited to participate. Patients who are enrolled in the intervention group will receive every-other-day administration for 16 weeks after 8 weeks of daily administration. Patients who are enrolled in the control group will receive daily throughout the 24 weeks. The primary outcome is the leiomyoma volume reduction, and the secondary endpoints are the reduction of uterine volume, the occurrence of the climacteric disorder, genital bleeding days, change rate of serum hormone or bone turnover markers, and bone mineral density after 24 weeks compared to before administration.

**Discussion:**

This study aims to prove both the non-inferiority in leiomyoma volume reduction and superiority in adverse effects occurrence reduction, which will provide a novel method to escape adverse effects while maintaining the effect of leiomyoma reduction.

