### Objectives {7}

This trial aims to prove the non-inferiority of leiomyoma reduction effect and safety evaluation (i.e., reduction of side effects) by every-other-day administration for 16 weeks after 8 weeks of everyday administration compared to throughout the duration.

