### Outcomes {12}

The primary endpoint will be the reduction of leiomyoma volume before and after the administration of relugolix. The secondary endpoints will be the reduction (%) of uterine volume compared with pre-treatment, change (score) of total Kupperman Index score at 24 weeks compared with pre-treatment, change rate (%) of bone mineral density (BMD) at 24 weeks compared with the baseline, and change rate (%) of bone metabolism markers(serum BAP) at 24 weeks compared with the baseline. The investigative assessments will be the total number of days of genital bleeding and the change in gonadotropic and sex hormone levels such as luteinizing hormone (LH), follicle-stimulating hormone (FSH), estradiol (E2), and progesterone (P4) at 24 weeks compared with the baseline. The MRI scans will be outsourced to another hospital, and tumor and uterine volume will be evaluated by the radiologist in the hospital with blind.

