## Statistical methods

### Statistical methods for primary and secondary outcomes {20a}

The assessment of primary endpoint will be assessed as follows: we defined the null hypothesis as “The mean rate of change in the intervention group is more than 20% inferior to the mean rate of change in the control group,” and this will be tested with a one-sided *t*-test at a significance level of 2.5%. In addition, 95% confidence intervals for the mean rate of change are calculated for each group and for the difference between the groups. The assessment of the secondary endpoint will be analyzed as follows. (1) Change in uterine volume from before study drug administration at 24 weeks after study drug administration (%). The measured values before the start of treatment and at 24 weeks and the rate of change at 24 weeks will be summarized for each group using descriptive statistics. The 95% confidence interval of the difference between the groups will be calculated for the mean of the rate of change. (2) Change in the total score of the Kupperman Index from before the study drug administration at 24 weeks after the study drug administration (points). (3) Percent change in bone mineral density (BMD) from baseline at 24 weeks post-treatment (%). The measurements before and at week 24 of treatment and the percent change at week 24 of treatment will be summarized for each group by descriptive statistics. In addition, the null hypothesis “the mean rate of change for the intervention group is equal to the mean rate of change for the control group” will be tested with a two-sided 5% *t*-test at the significance level. In addition, 95% confidence intervals for the mean rate of change will be calculated for each group and for the difference between the groups. (4) Percentage change in bone metabolism markers (serum BAP) at 24 weeks after treatment compared to before treatment with the study drug (%). The measured values before the treatment and at 8 and 24 weeks of treatment, and the change (%) at 8 and 24 weeks of treatment will be summarized for each group using descriptive statistics, and a graph of the mean ± standard deviation will be prepared for each time point. The null hypothesis “the mean of the amount (rate) of change in the intervention group is equal to the mean of the amount (rate) of change in the control group” is tested with a two-tailed *t*-test at a significance level of 5%. In addition, 95% confidence intervals for the mean of the amount (rate) of change will be calculated for each group and for the difference between the groups. Data for each endpoint will be analyzed after the period for collecting the data has ended and the data have been fixed. The intermediate analysis will not be performed.

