In conclusion, if this study confirms the non-inferiority of the primary endpoint and the superiority of the secondary endpoints of relugolix 40 mg/day for 8 weeks followed by every other day for 16 weeks compared to the standard treatment of 24 consecutive weeks, a novel protocol that can contribute both of the better economic prowess and the less burdensome for patients.

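### The plan sets out to prove superiority in how often adverse effects occur, but it analyses only mean changes and names no endpoint that decides superiority

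*Protocol article*

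**What the plan says.** All places are in the protocol article.

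**The aim.** The Discussion paragraph of the abstract states: "This study aims to prove both the non-inferiority in leiomyoma volume reduction and superiority in adverse effects occurrence reduction". Objectives {7} is milder: "This trial aims to prove the non-inferiority of leiomyoma reduction effect and safety evaluation (i.e., reduction of side effects", with no mention of superiority. The last paragraph of the main Discussion makes the conclusion conditional: "if this study confirms the non-inferiority of the primary endpoint and the superiority of the secondary endpoints".

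**The endpoints.** The Methods paragraph of the abstract lists "the occurrence of the climacteric disorder" among the secondary endpoints. Outcomes {12} has no such item. In its place stands "change (score) of total Kupperman Index score at 24 weeks compared with pre-treatment", next to percentage changes in uterine volume, BMD and serum BAP.

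**The analysis, in Statistical methods {20a}.**
- Uterine volume: descriptive statistics and a confidence interval, no test.
- Kupperman: a title only, "2) Change in the total score of the Kupperman Index from before the study drug administration at 24 weeks" and so on, with no analysis text of its own.
- BMD: a two-sided 5% t-test of equal means.
- BAP: equality of means "is tested with a two-tailed *t*-test at a significance level of 5" per cent. The title gives week 24. Summaries are planned at weeks 8 and 24. The test sentence names no week.

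**Events.** Adverse event reporting and harms {22} lists four safety endpoints (depression, grade 4 hepatic dysfunction, angina pectoris, grade 4 anemia) without a between-arm comparison. Under Plans for assessment {18a}, the presence of adverse effects is checked monthly. The Kupperman questionnaire is given at baseline, week 8 and week 24.

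**The concern.** Better tolerability is half of the trial's rationale: the sparser regimen is worth adopting only if it keeps the volume effect and spares patients side effects. The abstract frames the second half as something to be proved, and about occurrence. Occurrence means a comparison of how many patients have an event. The stated analysis compares mean scores and mean percentage changes. A lower mean Kupperman score can support a statement about symptom burden, but it does not show that fewer patients had adverse effects.

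The plan also does not say what would count as superiority. The closing paragraph refers to the secondary endpoints as a group. It does not say which of them, or whether all must succeed or any one would do. Read literally, the group includes uterine volume, for which no test is stated. With the rule open, the reading could be settled after the results are known.

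**Working it through.** **1. The plan's own sample size reproduces, and it covers only the primary test.** Inputs from Sample size {14}: margin 20, assumed changes −41 and −36 (true difference 5), SD 30, one-sided 2.5%, power 80%.

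n per arm = 2 × (1.960 + 0.842)² × 30² / (20 − 5)² = 62.8, so 63 by the normal approximation. With the t distribution, power is 79.5% at 63 and 80.1% at 64, so the stated 64 is right. No power is stated for any adverse-effect endpoint.

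**2. Aim against analysis.**

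| Place | Quantity | Between-arm comparison |
|---|---|---|
| Abstract, Discussion | occurrence of adverse effects | said to be proved superior |
| Abstract, Methods | occurrence of climacteric disorder | listed as endpoint |
| Outcomes {12}, Statistical methods {20a} | Kupperman change, points | test unclear |
| same | BMD change, % | two-sided 5% t-test |
| same | serum BAP change, % | two-sided 5% t-test |
| same | uterine volume change, % | confidence interval only |
| Harms {22} | four event types | none stated |

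No row has both an occurrence endpoint and a stated comparison.

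**3. How many tests.** Two are explicit (BMD, BAP). Kupperman would be a third if it shares the text that follows the BMD title. That text is worded for a rate of change, whereas Kupperman change is in points.

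**4. Error rate if any one success is enough.** For k independent tests, P(at least one false positive) = 1 − 0.95^k. In the favourable direction it is 1 − 0.975^k.

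- k = 2: 1 − 0.95² = 9.75%; favourable 1 − 0.975² = 4.9%.
- k = 3: 1 − 0.95³ = 14.3%; favourable 1 − 0.975³ = 7.3%.

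A single test gives 5% and 2.5%. Correlation lowers the figures. The documents give no correlation, so these values are assumed and simulated:

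| Assumed correlation | 2 tests, any | 3 tests, any | 2 tests, favourable | 3 tests, favourable |
|---|---|---|---|---|
| 0.5 | 9.1% | 12.5% | 4.5% | 6.2% |
| 0.8 | 7.8% | 9.8% | 3.9% | 4.9% |

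**5. Error rate if all must succeed.** A false claim then requires every tested endpoint to cross its threshold, so its chance cannot exceed that of a single test. There is no inflation.

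**6. Could the listed events carry the aim?** Harms {22} puts depression below 1%. With 1% against an assumed 0.5% and 64 per arm, power is about 5%, and 4,673 per arm would be needed for 80%. Commoner symptoms differ: with assumed rates, power is 84% for 50% against 25%, 64% for 50% against 30%, and 53% for 30% against 15%.

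**7. What a single mean-change endpoint can detect.** At 64 per arm, two-sided 5% and 80% power: (1.960 + 0.842) × √(2/64) = 0.50 SD. The documents give no SD for Kupperman change, so this cannot be converted to points.

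**The case against.** The strongest reply is that this is a condensed article. Multiplicity rules and adverse-event tabulations are commonly left to the statistical analysis plan, which Methods for additional analyses {20b} mentions and which is not shown. The formal objective speaks only of a safety evaluation, the design is labelled a non-inferiority assessment, and the closing sentence is conditional. Kupperman change is plausibly the working form of the abstract's climacteric endpoint.

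Much of this stands. The absence of an adjustment or testing order is not by itself an error in this document. An unseen plan could not, however, reconcile an abstract that promises proof about occurrence with Outcomes and Statistical methods sections that analyse something else. Those texts are all present, and they disagree.

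Four stronger readings are tempting and not supported:
- **That adverse effects are ignored or never compared.** Continuous measures of harm are analysed, and events are collected. What is missing is a stated between-arm comparison of occurrence.
- **That three 5% tests are specified, so 14.3% is the plan's error rate.** Only two are explicit, and any inflation requires that one success suffices. The plural in the closing paragraph can be read as requiring all.
- **That BAP will be tested at week 8.** Both arms follow the same regimen to day 56, so such a test could show only chance. But week 8 appears only in the sentence on summaries and the graph.
- **That climacteric events are already recorded monthly.** Only the presence of adverse effects is checked monthly. No climacteric event is defined, and the Kupperman questionnaire is given at three time points.

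**Conclusion.** The concern holds as an internal contradiction. The declared aim, "superiority in adverse effects occurrence reduction", has no matching comparison in the stated analysis, and no endpoint is designated to decide superiority. This rests on the text alone and needs no assumption about the missing analysis plan.

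The multiplicity part is secondary and conditional. If any one success counted and the tests were independent, the chance of at least one false positive would be 9.75% on the two explicit tests and 14.3% if Kupperman is a third, or 4.9% and 7.3% in the favourable direction. Positive correlation would make it smaller, and requiring all to succeed would remove it. That a lone significant result would be presented as proof is something a reader might fear; the documents do not say so.

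The primary non-inferiority test and its sample size are unaffected. What is at stake is the trial's second headline claim, which cannot be supported as now worded. It should be corrected before the data are analysed.

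**What to change.** 1. Name change in total Kupperman score at week 24 as the single superiority endpoint. It is the analysed measure closest to the climacteric symptoms on which the rationale rests. State its two-sided 5% test explicitly, in points, and run it only if non-inferiority on leiomyoma volume is shown.
2. Treat BMD and BAP at week 24 as supportive, or test them in a fixed order after Kupperman. The order between these two is a matter of preference. State that week-8 BAP is descriptive only.
3. Reword the abstract (Methods and Discussion paragraphs) and the closing paragraph of the main Discussion, so that occurrence and group-wide superiority give way to the named endpoint.
4. Report the adverse effects already recorded monthly by arm, with a risk difference and confidence interval, labelled descriptive.

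If no confirmatory tolerability claim is wanted, removing the superiority wording would also resolve the contradiction.

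**Cost.** Wording in the protocol and analysis plan; no change to treatment, data collection or sample size. The downside is that BMD and BAP could no longer be claimed as proven superiority on their own. Kupperman is also a questionnaire in an open-label trial, which should be acknowledged when the result is interpreted.

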**Trial registration:**

Japan Registry of Clinical Trials jRCTs051230078. Registered on 26 July 2023.

## Introduction

### Background and rationale {6a}

Uterine leiomyomas are commonly detected with a prevalence reaching up to 60% of reproductive-aged women [1, 2] and affect women’s quality of life due to heavy menstrual bleeding or dysmenorrhea [3–5]. Leiomyomas grow according to estradiol exposure and decrease after post-menopause [6, 7]. In clinical practice, pharmacotherapy or surgical treatment is proposed for serious symptoms like abdominal distension, dysuria, infertility, or severe anemia due to heavy menstrual bleeding caused by leiomyomas. In the case of pharmacotherapy, a gonadotropin-releasing hormone (GnRH) receptor agonist (i.e., leuprorelin acetate or goserelin acetate) has been used to pause the menstrual cycle [8]. However, it induces a transient increase in gonadotropins and sex hormones, resulting in a clinical flare-up or temporary worsening of symptoms, and typically takes about 4 weeks to achieve a therapeutic effect [3, 9]. GnRH receptor antagonists (i.e., relugolix, elagolix, or linzagolix) are also used as newer treatments for uterine leiomyomas [10, 11]. Relugolix is a new orally active small molecule GnRH receptor antagonist [12–14] which proved its sufficient efficacy to suppress estradiol without the transient estradiol flare-up compared with GnRH agonist [15, 16]. However long-term administration should not be permitted liable to for climacteric disorder or osteoporosis. In the case of surgical treatment, pharmacotherapies like GnRH agonists or antagonists aimed at the reduction of leiomyoma and uterine volume or improvement of anemia are also introduced before the surgical treatment to conduct less invasive surgery (i.e., to reduce blood loss or surgical duration). However, the clinician often encounters cases in which menopausal symptoms are thought to be drug-related at about 8 weeks after the beginning of treatment, making it difficult to continue treatment [17]. Since the phase III trial was designed for relugolix administration to patients with leiomyoma, the leiomyoma volume as a secondary endpoint was reduced by 43.28 ± 33.85% by 12 weeks and 49.75 ± 34.33% by 24 weeks of administration compared with the baseline; we have hypothesized that everyday administration for 8 weeks and subsequently every-other-day administration of relugolix only for maintaining the effect could be a compatible method [18].

### Objectives {7}

This trial aims to prove the non-inferiority of leiomyoma reduction effect and safety evaluation (i.e., reduction of side effects) by every-other-day administration for 16 weeks after 8 weeks of everyday administration compared to throughout the duration.

### Trial design {8}

This is a phase IV study designed as a randomized, parallel-group comparative trial, with a 1:1 allocation for non-inferiority assessment.

## Methods: participants, interventions, and outcomes

### Study setting {9}

This will be a minimization adaptive randomized control trial, at the Nara Medical University Hospital in Nara, Japan. The study was conducted in accordance with the principles outlined in the Declaration of Helsinki, the International Council for Harmonization Guideline for Good Clinical Practice, and all applicable local regulatory requirements. The study, including the protocol and informed consent form, was approved by the Nara Medical University Certified Review Board (Approval Number: CRB5200002). Registration is from September 25, 2023, to August 31, 2024. The observation period will last until February 28, 2025, and the study is scheduled to end on August 31, 2025. Each patient will be provided informed consent before undergoing any study-related procedures. In the case of the study protocol modification, the information will be noticed and confirmed after approval by the review board and the Japan Registry of Clinical Trials (jRCT) modification.

### Eligibility criteria {10}

#### Inclusion criteria

These are the requirements for participating in the study: the participant must have been diagnosed with uterine myoma, be scheduled to undergo an abdominal or laparoscopic hysterectomy or myomectomy, be a pre-menopausal female between 20 and 51 years old, can provide written consent of her own free will, and have an ECOG-PS1 rating or lower. ECOG-PS1 is a condition that limits strenuous activity but allows walking, light or sedentary work. However, it does limit strenuous activity (Fig. 1).

**Fig. 1 Fig1:**
[figure not shown]
Patient disposition chart showing study participation. Of randomized patients, 70 patients will be included in the control group as the continuous administration, and the other 70 patients in the intervention group as the other day administration after 8 weeks every day of relugolix. PS, performance status

#### Exclusion criteria

Patients with the following factors will be excluded: adenomyosis, administration of sex steroid hormone within 4 weeks with informed consent, history of uterine artery embolism or focused ultrasound surgery, diagnosed as a malignant tumor, diagnosed as a disease of abnormal blood coagulation, undertreatment of an anticoagulant agent, pregnant or susceptible to pregnancy or in lactation; abnormal genital bleeding without a diagnosis, allergy history to relugolix or synthetic luteinizing hormone-releasing hormone (LH-RH) or LH-RH derivatives, patients who are continuously taking erythromycin or rifampicin, or others which principal investigator or collaborator decided as not appropriate (Fig. 1).

### Who will take informed consent? {26a}

The principal investigator/participating physician will give the patient an informed consent form including an explanatory document describing the research and explain it in accordance with the form. After explaining the research, giving the patient sufficient time to think about it, and confirming that the patient fully understands the content of the research, the patient will be asked to participate in the study. If the patient agrees to participate in the study, the consent document will be signed by the patient herself. One copy of the consent document will be kept by the site, and one copy will be given to the patient.

### Additional consent provisions for collection and use of participant data and biological specimens {26b}

Depending on the nature of the research, it will be conducted after review and approval by the relevant Ethics Review Committee and permission by the administrator of the implementing medical institution and after a separate explanation to the patients.

### Interventions

#### Explanation for the choice of comparators {6b}

The control group is taking 40 mg of relugolix every day for 24 weeks.

#### Intervention description {11a}

The initial dose of relugolix is 40 mg orally once daily before meals, starting on days 1–5 of the menstrual cycle until day 56. On day 57, the control group will continue taking 40 mg of relugolix every day, and the intervention group will switch to 40 mg of relugolix every other day. However, change to another group will not be permitted.

#### Criteria for discontinuing or modifying allocated interventions {11b}

The criteria for discontinuing are as follows: (1) If the subject declines to participate in the study or withdraws consent; (2) If the subject is found to be ineligible after enrollment; (3) If the primary illness is completely cured by emergency surgery or other means and there is no longer a need for continued administration; (4) If the subject has persistent heavy genital bleeding due to deterioration of the primary illness and anemia of grade 3 or higher as defined in CTCAE v5.0 Grade; (5) The following serious adverse reactions associated with study drug administration are observed. Depression: when the patient does not respond to psychiatric treatment and the main cause is considered to be the study drug. Hepatic dysfunction: AST/ALT levels of grade 2 or higher in the CTCAE v5.0 Grade definition. Angina pectoris: diagnosed during the period of study drug administration; (6) Exacerbation of side effects associated with study drug administration that makes continuation of study drug administration inadvisable; (7) If the subject develops hypersensitivity to the study drug itself; (8) If the subject becomes pregnant; (9) If the subject’s medication adherence is extremely poor or over (< 70% of the total scheduled doses or > 120% of the total scheduled doses); (10) The subject fails to come to the hospital due to relocation or other reasons and is unable to receive relugolix for more than 8 weeks; (11) The entire study is terminated; (12) The physician deems it appropriate to terminate the subject’s continued participation in the study for other reasons; and (13) If the subject has any of the following serious adverse reactions to the study drug.

